### Medication adherence

All patients discharged during the treatment period (< 5 days) will be contacted in order to confirm whether the prescribed medication has been taken. This is to control for adherence with prescribed medication and to keep an accurate record of doses of medication for each patient.

### Withdrawal of study

In general, no subject should be removed from the study for a protocol violation prior to confirmation by the coordinating investigator. A patient is only to be withdrawn from the study if the participant explicitly asks for withdrawal.

### Size of the study population and statistical considerations

Data will be analysed using intention-to-treat (ITT) principles, including all the data available regardless of whether the intervention is completed. The aim of the ITT analysis is also to provide unbiased comparisons among groups and avoid the effects of dropout and handle patients who deviates from the protocol, e.g. intubated patients during their hospitalization.

Patients in SC will be compared to patients with eosinophil guided prednisolone sparing therapy (Intervention group). The mean LOS (μ = 8) and standard deviation (σ = 3.81 days) after a hospitalization for AECOPD is estimated based on previous studies comparing systemic corticosteroids versus placebo [3, 19]. A two-sided 95%-confidence interval will be computed for the difference in LOS in the intervention group minus standard care group. We will accept a null hypothesis if the LOS in the intervention group does not exceed 1.2 days of the average LOS in the SC arm. The probability that the study will detect a treatment difference is 80% at a two-sided 5% significance level. This provides a sample size of 320 subjects. Sample-size calculation has been performed by using SAS software (version 9.4).

The results are expressed in mean (days) and SD if data is normally distributed, or as median (IQR). Data will be analysed using SAS software.

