## Methods

### Objective

The overall objective is to determine whether a prednisolone regimen with lower accumulated doses in hospitalised patients with AECOPD have noninferior clinical outcome than when applying standard care (SC). Based on a sufficiently sized (powered) clinical study, the aim is to determine if there is no relevant increase in LOS for AECOPD patients receiving eosinophil guided prednisolone-sparing therapy compared to SC. The primary endpoint of this analysis is LOS defined as the time from hospital admission to hospital discharge within 14 days after recruitment. The secondary objective is to determine if the clinical outcome for patients receiving eosinophil guided corticosteroid-sparing therapy will not be less favourable compared to SC. The following endpoints will be included when assessing the clinical outcome: 30-day mortality rate, treatment failure, COPD related re-admission rate, changes in FEV_1_, changes in health-related quality-of-life measured by COPD Assessment Test (CAT), changes in level of dyspnoea using the modified Medical Research Council (mMRC) Dyspnoea Scale, cumulative systemic corticosteroid dose, the period between index AECOPD and the next AECOPD and a number of adverse effect measures between index hospitalization and 3 month follow-up. The adverse effect measures include hyperglycemia, osteopenia (Bone Turnover Markers: C-terminal telopeptide of type 1 collagen (CTX) and procollagen type 1 N propeptide (P1NP)), osteoporotic fractures, dyspepsia or ulcer complications (gastrointestinal bleeding), onset of diabetes mellitus (defined as HbA1c ≥ 48 mmol/mol) or worsening of diabetes mellitus (defined as initiation/intensification of anti-diabetic treatment), increase in Body Mass Index and new infections treated with antibiotics since study entry.

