### Measurements

All outcome measures will be recorded at baseline and at the one and three month follow up visits (Table 1). On the baseline visit (during hospitalization), the following variables will be noted: sociodemographic data (e.g. sex, age, height, weight, ethnicity), smoking history, pack-years, co-morbidities (including the presence of diabetes, heart failure, ischemic heart disease, atrial fibrillation, essential hypertension, hypercholesterolemia), employment status, support with activities of daily living at home, clinical symptoms (increased dyspnea, increased sputum volume, and increased sputum purulence (Anthonisen criteria), increased cough), disease symptoms duration, body mass index (kg/m^2^), number of exacerbations in the past, atopy status, mean cumulative systemic corticosteroid dose (mg) 4 weeks before study entry, use of oxygen therapy, use of noninvasive mechanical ventilation, vital signs, adverse events to systemic corticosteroids, medication adherence by day 5, arterial blood gases and Ca^2+^, blood samples, findings from Chest X-ray and spirometry will be collected and stored on Case Report Forms in pseudoanonymised format at the treatment site (Table 1). Furthermore, patients will be requested to complete the CAT and mMRC Dyspnoea Scale. Follow-up visits will be conducted one and three months after discharge. If the patient does not attend the visit, the patient will be contacted for a new follow-up or - if not able to meet for an appointment at the hospital - a home visit by a doctor assigned to the project. At the one month and the three month follow up visits the following data will be assessed: BMI, HbA1c (only at the one month follow-up), spirometry values, CAT score, mMRC, CTX, P1NP, PTH (only at the three month follow-up), D-vitamin status (only at the three month follow-up), cumulative systemic corticosteroid dose, the period between index AECOPD and the next AECOPD, COPD related re-admission rate, dyspepsia or ulcer complications (gastrointestinal bleeding) and new infections treated with antibiotics since study entry.

**Table 1 Tab1:** Data collected at baseline and follow-up visits

Data collected	Study period		
	Baseline	1-month	3-month
Demographics	X		
Daily blood glucose measurements	X		
Daily leukocyte differential count^a^	X		
Arterial blood gases and Chest X-ray	X		
Testing for diabetes (HbA1c)	X	X	
Spirometry	X (day 1 + day 3)	X	X
Height measurement & vital signs	X		
Weight measurement	X	X	X

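### The primary length-of-stay comparison names no baseline covariates although likely predictors are recorded; prespecified adjustment would be a nearly free efficiency gain

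*Protocol article*

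**What the plan says.** The primary endpoint is "LOS defined as the time from hospital admission to hospital discharge within 14 days after recruitment" (Objective). The analysis is given under Size of the study population and statistical considerations: "A two-sided 95%-confidence interval will be computed for the difference in LOS in the intervention group minus standard care group". Non-inferiority is accepted if LOS in the intervention group "does not exceed 1.2 days of the average LOS in the SC arm". The sizing input is "The mean LOS (μ = 8) and standard deviation (σ = 3.81 days) after a hospitalization for AECOPD is estimated based on previous studies", the power "is 80% at a two-sided 5% significance level", and the conclusion "This provides a sample size of 320 subjects".

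That section names no regression model, no covariate and no use of the randomisation strata. It does not call the difference unadjusted, and it does not exclude adjustment.

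Randomisation is stratified by site (four departments) and by age around 70 years (Study design, randomization and intervention). No measure of severity is a stratification factor.

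The Measurements section lists many baseline items. They include "use of oxygen therapy, use of noninvasive mechanical ventilation, vital signs", "support with activities of daily living at home", arterial blood gases, spirometry, comorbidities and the number of past exacerbations.

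**The concern.** Non-inferiority depends on where the upper confidence limit falls relative to 1.2 days, so the width of the interval matters directly. Acute severity and circumstances at home plausibly influence when a patient can be discharged. If they do, part of the 3.81-day SD is predictable from information the trial already plans to collect. Leaving that part in the residual makes the interval wider than necessary.

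Prespecification matters too. The trial is open-label, and the principal investigator conducts the analysis (end of Measurements). If the baseline table shows a visible difference in, say, ventilation use and no covariates were named beforehand, any later adjustment can be challenged as chosen to suit the result, whichever way it moves.

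**Working it through.** **Inputs from the protocol article.** Margin 1.2 days, SD 3.81 days, two-sided 5% (one-sided 2.5% for non-inferiority), power 80%, 1:1 allocation, N = 320. A true difference of zero is assumed.

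**Step 1: reproduce the stated size.** By the normal approximation, n per arm = 2 × 3.81² × (1.96 + 0.842)² / 1.2² ≈ 158.2, rounded up to 159, or 318 in total. The noncentral t calculation gives 160 per arm, 320 in total, with power 80.2%. The stated 320 therefore reproduces, and it corresponds to a comparison using the full, unadjusted SD.

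**Step 2: planned precision.** SE = 3.81 × √(2/160) = 0.426 days. Half-width = 1.96 × 0.426 = 0.835 days. Power by the normal approximation is 80.4%.

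**Step 3: effect of adjustment.** If prognostic baseline variables explain a share R² of LOS variance, the residual SD is 3.81 × √(1 − R²), and SE and half-width shrink by the same factor. The article gives no R², so a range is assumed. Power and N use the normal approximation.

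| Assumed R² | SE (days) | Half-width (days) | Narrower by | Power at N = 320 | N for 80% power |
|---|---|---|---|---|---|
| 0 | 0.426 | 0.835 | – | 80.4% | 318 |
| 0.05 | 0.415 | 0.814 | 2.5% | 82.4% | 302 |
| 0.10 | 0.404 | 0.792 | 5.1% | 84.4% | 286 |
| 0.20 | 0.381 | 0.747 | 10.6% | 88.3% | 254 |

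These figures ignore the small cost of estimating the covariate coefficients. For five severity variables that cost is roughly a factor √(1 + 5/312) ≈ 1.008 on the SE, which is one reason to keep the list short.

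**Step 4: what a chance imbalance does.** If a severity score explains R² of LOS variance, a one-SE imbalance between arms shifts the unadjusted difference by √R² × 0.426. That is 0.095, 0.135 or 0.190 days for R² of 0.05, 0.10 or 0.20. At 1.96 SE the shift is 0.187, 0.264 or 0.373 days. This variation is a component of the 0.426-day SE and not an addition to it. For R² = 0.20, 0.190² + 0.381² = 0.036 + 0.145 = 0.181, which equals 0.426² to rounding. Adjustment removes the first component.

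**Step 5: which recorded items qualify.** Not everything listed at baseline can serve as a covariate. Adherence by day 5 and day-3 spirometry come after randomisation. The daily differential count is made in the intervention group only (Table 1 footnote). The baseline visit takes place during hospitalisation, and its timing relative to randomisation is not stated, so each covariate needs an explicit rule on timing.

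**The case against.** The strongest reply is that nothing here is wrong. The sentence on the confidence interval fits an adjusted difference as well as an unadjusted one. A journal article condenses the full protocol, and covariate lists are commonly left to the statistical analysis plan, which is not shown. The trial reaches its stated power without covariates. The gain rests on an R² that appears nowhere in the article, and at R² = 0.05 the half-width falls by only about 0.02 days. Patients needing invasive ventilation or ICU admission are excluded, which narrows the range of severity and may lower R².

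Most of this stands, and it sets the limits of the point. It cannot be said that the plan rules out adjustment, that the trial is underpowered, or that the gain is known to be large.

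A reader might also infer that, because severity is not a stratification factor, a chance imbalance makes the estimate biased or raises the risk of a false non-inferiority claim. The documents do not support that. Randomisation balances severity in expectation, the unadjusted difference is unbiased, and its interval already allows for chance imbalance (Step 4). Over all randomisations the one-sided error stays at 2.5%.

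What the objection does not remove is this. The article states an estimator, sizes the trial on the unadjusted SD, and plans to collect variables that could improve that estimator without changing the endpoint, the margin or the target quantity. That makes it a specific improvement to a stated method and not a complaint about missing detail.

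**Conclusion.** The point holds as a missed efficiency gain. As described, the primary analysis is a between-arm difference in LOS with no covariates named, and its sample size matches an unadjusted comparison. That analysis is valid and adequately powered on its own assumptions. Prespecified adjustment would narrow the half-width of about 0.84 days by about 2.5% to 11%, and raise power from 80% to about 82% to 88%, for R² between 0.05 and 0.20. The size depends wholly on that assumed range and is modest at its lower end. A further benefit, which does not depend on R², is that naming the covariates beforehand settles how any visible imbalance will be handled.

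**What to change.** Prespecify that the primary estimate and its two-sided 95% confidence interval come from a linear model for LOS with terms for arm, site, age group (the randomisation strata) and a short named list of severity variables already on the case report form. Candidates are non-invasive ventilation, arterial pH or pCO2, FEV1, support at home and number of past exacerbations.

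Use only values recorded before randomisation, because in an open-label trial anything recorded later could be affected by knowledge of the allocation. State a simple imputation rule for missing covariate values so that no randomised patient is dropped on their account.

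Compare the adjusted upper limit with 1.2 days and report the unadjusted difference beside it. The model still estimates a mean difference in days, so the margin is unchanged.

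The cost is a sentence or two of analysis wording, settled before outcome data are examined. It needs no extra patients, visits or measurements, provided the pre-randomisation timing of each chosen item can be confirmed. If the statistical analysis plan already specifies such adjustment, confirm it there and nothing further is needed.

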## Discussion

COPD is a heterogeneous disease and is, by that, also associated with different responses to systemic corticosteroids for acute worsening of the disease. Although systemic corticosteroids improve some clinical outcomes in AECOPD - such as LOS, FEV_1_ on day 3, treatment failure and re-exacerbation rate the first month - the magnitude of benefit is small and probably restricted to subgroups of patients [3].

The novel aspect of this study is to investigate non-inferiority of eosinophilic guided corticosteroid-sparing therapy against the current standardized treatment of 5 days to all AECOPD patients. The study investigates whether the accumulated dose of systemic corticosteroid treatment during admissions for AECOPD can be reduced, including the presumed side effects, while simultaneously attaining the optimal treatment effect. Studies have shown that systemic corticosteroids improve outcome in exacerbations associated with either serum eosinophil counts equal to or above 2% [16] or eosinophil counts equal to or above 0.34 10^9^ cells/L [20]. However, on the other hand, this therapy might be detrimental in those with lower eosinophil counts [16]. A recent retrospective study has found that blood eosinophil-positive (eosinophilia ≥2%) severe AECOPD require a lower daily dose of systemic corticosteroids during hospitalization compared to blood eosinophil-negative (eosinophilia <2%) AECOPD. Thereby, the study concludes that the group with blood eosinophil-positive severe AECOPD respond better to systemic corticosteroids. Moreover, the former group had a shorter LOS (geometric mean 8.9 ± 1.5 versus 11.3 ± 1.5 days, respectively; *p* = 0.028) [21]. The result was supported by another sub-group analysis within a large randomized clinical trial which found shorter LOS in the group with eosinophilic (blood eosinophil count ≥200 cells/μL and/or ≥2% of the total leukocyte count) associated exacerbations (mean (range) 5.0 (1–19) vs. 6.5 (1–33), *p* = 0.015) following treatment with systemic corticosteroids [22].

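### The primary decision rule is misworded for a non-inferiority trial: it accepts an undefined null hypothesis, leaves the 95% interval unlinked to the 1.2-day margin, and describes power as detecting a difference

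*Protocol article*

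**What the plan says.** The aim is non-inferiority. Under Objective, the lower-dose regimen is to "have noninferior clinical outcome than when applying standard care (SC"), and the Discussion says: "The novel aspect of this study is to investigate non-inferiority of eosinophilic guided corticosteroid-sparing therapy". The primary endpoint is "LOS defined as the time from hospital admission to hospital discharge within 14 days after recruitment".

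The section on size of the study population and statistical considerations then gives, in this order:

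- the planning values: "The mean LOS (μ = 8) and standard deviation (σ = 3.81 days");
- the interval: "A two-sided 95%-confidence interval will be computed for the difference in LOS in the intervention group minus standard care group";
- the decision rule, which is to "accept a null hypothesis if the LOS in the intervention group does not exceed 1.2 days of the average LOS in the SC arm";
- power: "The probability that the study will detect a treatment difference is 80% at a two-sided 5% significance level";
- the resulting sample size, 320.

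The null hypothesis is not defined, and no sentence says which limit of the interval is compared with 1.2 days.

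**The concern.** Three parts of the primary rule do not fit a non-inferiority test.

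1. **Direction of the hypothesis.** The null should be that the intervention lengthens stay by at least the margin, and the data must reject it. Here success consists of accepting a null that is left undefined.
2. **Criterion.** The sentence sets LOS in one arm against the average in the other. It does not mention the interval announced just before it, so it can be read as a rule about the observed means.
3. **Power.** A chance of detecting a difference belongs to a superiority test. Next to an instruction to accept a null, it invites treating a non-significant difference as success.

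This is the only decision rule for the primary endpoint in the article. If the analysis followed either faulty reading, the trial could claim non-inferiority on data that do not exclude 1.2 extra days in hospital.

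**Working it through.** **Inputs.** SD 3.81 days, margin 1.2 days, 80% power, two-sided 5% level and N = 320 all come from the statistical section. The 1:1 allocation, from the design section, gives 160 per arm. The true difference assumed for power is not stated; 0 is inferred.

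**Step 1: reproduce the sample size.** For non-inferiority with margin 1.2, one-sided 2.5% and true difference 0:

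n per arm = 2 × (1.960 + 0.842)² × 3.81² / 1.2² = 158.2, so 159 per arm (318 in total).

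The t-based version gives 160 per arm, exactly 320. Power at 160 per arm is 80.4% (normal) or 80.2% (t). A superiority calculation for a 1.2-day difference at two-sided 5% also gives 159 per arm, so N cannot show which test was meant. A one-sided 5% level gives 125 to 126 per arm, about 250 in total, and does not reproduce 320.

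**Step 2: precision at the planned size.**

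- SE = 3.81 × √(2/160) = 0.426 day
- 95% half-width = 1.96 × 0.426 = 0.835 day
- Largest observed difference that keeps the upper limit below 1.2: 1.2 − 0.835 = 0.365, about 0.37 day

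**Step 3: false non-inferiority at a true excess of exactly 1.2 days** (normal approximation).

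| Reading of the rule | Calculation | Rate |
|---|---|---|
| Upper 95% limit below 1.2 | Φ((0.365 − 1.2)/0.426) = Φ(−1.96) | 2.5% |
| Observed difference at most 1.2 | Φ((1.2 − 1.2)/0.426) = Φ(0) | 50% |
| Difference not significant at two-sided 5% | Φ((0.835 − 1.2)/0.426) − Φ((−0.835 − 1.2)/0.426) | 19.6% |

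At a true excess of 1.5 days, the observed-difference reading still passes Φ((1.2 − 1.5)/0.426) = Φ(−0.70) = 24% of trials. The upper-limit rule passes Φ((0.365 − 1.5)/0.426) = Φ(−2.66), about 0.4%.

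**Step 4: an example result.** An observed difference of 0.8 day has a 95% interval of 0.8 ± 0.835, or −0.03 to 1.63. It succeeds under both faulty readings, being below 1.2 and not significant. It fails the upper-limit rule because 1.63 exceeds 1.2.

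**The case against.** The strongest reply is that the intended rule is plain. The interval for intervention minus standard care comes immediately before the 1.2-day sentence, its sign matches the direction of the margin, and no other use is given for it. The aim is stated as non-inferiority in two places, and 320 reproduces exactly as a non-inferiority calculation. The 1.2-day sentence never says observed difference, so it may be a clumsy statement of the hypothesis about the true means. The non-significance reading makes no use of the 1.2 days at all. The article also condenses a fuller protocol, and an analysis plan may exist.

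Much of this stands. The upper-limit rule was probably meant, and the spread of rates across readings shows that the text is unclear, not that the trial will run at 50%. A reader might infer that the plan as a whole fails to control the false non-inferiority rate. The documents do not support that: the inflated rates hold only under the faulty readings. Nor does the power wording make the sample size wrong. A reader might also count acceptance of a smaller true excess, such as 0.6 day, as a false conclusion. That is not one, because 0.6 day lies inside the margin.

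What the reply does not remove is that the article states a rule, and states it wrongly. Condensing explains a missing detail; it does not explain accepting a null hypothesis in a non-inferiority trial or giving a superiority power statement. Because the superiority formula gives the same N, the sample size cannot settle which rule applies.

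**Conclusion.** The primary decision rule is misstated and should be corrected, but the fault lies in the wording and not in the design. Endpoint, margin, direction of the difference, interval and sample size all fit a valid test with a 2.5% error rate. That test is simply not the one written down. The practical gap is between an observed difference of about 0.37 day, the most a valid claim allows, and 1.2 days, which the sentence can be read to allow. Because the trial is open-label, it is better to close this ambiguity before the outcome data are analysed.

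The figures assume the planning SD of 3.81 days, 160 analysed patients per arm and an approximately normal mean difference. The 50% and 20% rates are conditional on the two faulty readings.

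**What to change.** Replace the decision-rule and power sentences with text such as:

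> H0: mean LOS difference (intervention minus SC) ≥ 1.2 days; H1: < 1.2 days. Non-inferiority is concluded only if the upper limit of the two-sided 95% CI is below 1.2 days (one-sided 2.5%). With 160 per arm, SD 3.81 days and an assumed true difference of 0, the probability of concluding non-inferiority is about 80%.

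The sponsor should confirm the assumed true difference of 0, since it is inferred from the sample size and not stated in the article. Remove the phrases about accepting a null and detecting a difference, and use the same rule in any analysis plan.

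The cost is a change of wording. N stays at 320 and no extra patients or data are needed. The article reports recruitment as ongoing, so on its account the change can be made before the primary analysis.

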### Previous research

A more recent Cohrane review (13 studies contributed data, *n* = 1620) regarding AECOPD patients has shown that systemic corticosteroids (compared to placebo) reduce the risk of treatment failure (number needed to treat (NNT) = 9; 95% confidence interval (CI) 7 to 14). Treatment failure was defined as patients who within 30 days required hospitalization or emergency room visits or patients requiring add-on pharmacological maintenance therapy. The risk of recurrence of AECOPD was also reduced within the first month (hazard ratio (HR) 0.78; 95% CI 0.63 to 0.97), whereas no difference in AECOPD recurrence was observed during the following 3 months [3].

Lung function measured up to 72 h after first administration of systemic corticosteroids showed significant improvement in forced expiratory volume in 1 s (FEV_1_) in the corticosteroid group (mean difference (MD) 140 mL; 95% CI 90 to 200), whereas this difference was not observed at later time-points. No difference was observed in mortality (odds ratio (OR) 1.0; 95% CI 0.60 to1.66). The total length of hospital stay (LOS) was shorter in the corticosteroid-treated group (MD −1.22 days; 95% CI -2.3 to −0.2), whereas there was no difference in the LOS in intensive care unit. The risk of steroid induced side effects was, as expected, increased (OR 2.33; 95% CI 1.59 to 3.43) in the corticosteroid-treated group compared with the control group; number needed to harm (NNH) = 6; 95% CI 4 to 10). Meanwhile, the proportion of side effects in the corticosteroid group (48.1%) was considerably higher than the control group (28.5%). The risk of hyperglycemia was increased (OR 2.79; 95% CI 1.86 to 4.19) and the absolute risk was 28.2% [3]. Others have identified serious psychiatric side effects (depression, mood changes, psychosis) and serious somatic side effects such as hypertension, ulcers, secondary adrenal insufficiency, diabetes, osteoporosis and increased risk of bone fractures in patients exposed to long-term systemic corticosteroids [5–7].

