Earlier, the inflammatory process in patients with AECOPD was believed to be homogeneous, primarily neutrophilic. However, recent studies have shown that both inflammation [8, 9] and ethiology [10–12] are heterogeneous. It has been demonstrated that a subgroup of patients with AECOPD have eosinophilic inflammation [13]. Specific attention on biological clusters and biomarkers of these have resulted in an increased understanding of the differentiated inflammatory mechanisms that exist in AECOPD [14]. Examinations of sputum from the airways in smokers have increased this understanding further [15].

A small randomized study (*n* = 109) of COPD patients with moderate exacerbations has indicated that blood eosinophil-guided corticosteroid treatment might reduce the use of systemic corticosteroids in exacerbations by 49% without simultaniously worsening of symptoms and increasing risk of treatment failure compared with standard care [16]. Furthermore, patients with initial low eosinophil count more often experienced treatment failure if they had received corticosteroid therapy rather than if they had not (15% treatment failure in prednisolone group, 2% treatment failure in corticosteroid-saving group, *p* = 0.04). However, the study had no impact on current recommendations due to the limited sample size. Larger cohort studies documented that diagnosed COPD patients with daily symptoms have more than 3-fold increased risk for AECOPD if they have an eosinophil count ≥0.34 × 10^9^ cells/L [17].

So, the question that remains to be answered based on the currently available studies is whether the clinical effects of systemic corticosteroid treatment in hospitalised patients with AECOPD can be achieved via a more targeted and individualized eosinophil-guided treatment rather than the current “one-size fits all” treatment. To our knowledge, no randomized clinical trials have yet examined this field. This study will address this important question. The aim is to determine whether it is possible to reduce the use of systemic corticosteroids in AECOPD without influencing the outcome by applying a biomarker-guided strategy. Additionally, the study will explore whether this strategy reduces some of the most frequent side effects that occur with the current standard treatment.

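### Meeting the 1.2-day margin rules out an excess of that size but cannot show that the steroid benefit on length of stay is preserved

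*Protocol article*

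**What the plan says.** All places are in the protocol article.

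- **Aim.** The last paragraph of Previous research says the trial is to find out whether one can "reduce the use of systemic corticosteroids in AECOPD without influencing the outcome by applying a biomarker-guided strategy". The Abstract's background states the same aim.
- **Objective.** "the aim is to determine if there is no relevant increase in LOS for AECOPD patients receiving eosinophil guided prednisolone-sparing therapy" compared with standard care. The overall objective is framed as non-inferiority, and LOS is counted within 14 days of recruitment.
- **Criterion.** Under Size of the study population and statistical considerations, success is declared when the guided arm's LOS "does not exceed 1.2 days of the average LOS in the SC arm". A two-sided 95% confidence interval is computed for intervention minus standard care.
- **Planning values.** "The mean LOS (μ = 8) and standard deviation (σ = 3.81 days"), taken from studies of systemic corticosteroids against placebo, with 80% power, a two-sided 5% level and 320 patients.
- **Known effect of the comparator.** Previous research, on the same placebo-controlled evidence: "The total length of hospital stay (LOS) was shorter in the corticosteroid-treated group (MD −1.22 days; 95% CI -2.3 to −0.2").
- **Treatment contrast.** Under Study design, randomization and intervention, both arms receive the intravenous dose first. The intervention arm then receives tablets only on days with a count at or above 0.3 × 10⁹ cells/L.

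**The concern.** A non-inferiority margin fixes how much of the comparator's benefit may be lost before the new strategy is called worse. Here the allowed loss and the comparator's quoted benefit are the same number to rounding. A trial that just meets the rule has a confidence interval that reaches almost to the full steroid-versus-placebo difference.

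The primary result will be read through the stated aims. If success at 1.2 days is reported as showing that outcome is not influenced, or that LOS is not relevantly increased, the claim goes further than the criterion supports. The Discussion presents non-inferiority as the novel aspect of the study, so the meaning of the main conclusion is at stake.

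**Working it through.** **Inputs.** Margin 1.2 days, SD 3.81 days, 1:1 allocation of 320 patients (160 per arm), two-sided 5% (one-sided 2.5%), 80% power. Quoted steroid effect 1.22 days, 95% CI 0.2 to 2.3. I read the rule as requiring the upper limit of the two-sided 95% interval to lie below 1.2 days.

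**1. The plan's own figure.** With a true difference of 0:

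n per arm = 2 × (1.96 + 0.8416)² × 3.81² / 1.2² = 158.2, rounded up to 159, or 318 in total.

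The stated 320 reproduces. Power at 160 per arm is about 80%.

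**2. Margin against the quoted effect.**
- Against the point estimate: 1.2 / 1.22 = 98%. A true excess of 1.2 days would leave 0.02 of 1.22 days, about 2%.
- Against the limit nearest zero: 1.2 / 0.2 = 6.

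**3. What success requires in the data.**
- SE = 3.81 × √(2/160) = 0.426 days.
- Half-width = 1.96 × 0.426 = 0.83 days.
- Largest observed excess that passes = 1.2 − 0.83 = about 0.37 days.

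**4. Chance of declaring non-inferiority at a true excess δ:** Φ((1.2 − δ)/0.426 − 1.96). At δ = 1.22 this is 2.2%.

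**5. Illustration of dilution (assumed shares, not in the documents).** Suppose a fraction p of patients is treated the same in both arms and contributes no difference. An overall excess of 1.2 days then means 1.2/(1 − p) in the rest:
- p = 20%: 1.5 days
- p = 40%: 2.0 days

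If the rest lost the whole 1.22 days, the overall excess and the chance of passing would be:
- p = 20%: 0.8 × 1.22 = 0.976 days, 7.6%
- p = 40%: 0.6 × 1.22 = 0.732 days, 19.5%

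**6. A stricter supplementary reading at 0.6 days (about half of 1.22, a convention).**
- n per arm = 2 × (1.96 + 0.8416)² × 3.81² / 0.6² = 633, or 1,266 in total.
- Power with 160 per arm and no true difference = Φ(0.6/0.426 − 1.96) = 29%. It would be somewhat higher if the 14-day cap lowers the SD below 3.81.

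**The case against.** **Success is harder than the margin suggests.** An observed excess above about 0.37 days, roughly 30% of 1.22, fails. A true loss of the full effect would pass only 2.2% of the time. No margin above zero can show that an outcome is literally unaffected. All of this stands, and it is why the point concerns the conclusion and not the test or the sample size.

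**The protocol expects little loss in the patients from whom tablets are withheld.** Previous research cites more treatment failure with prednisolone than without it at low counts (15% against 2%). The Discussion says benefit is probably confined to subgroups. The 1.22 days is an average over all patients, and everyone gets the first intravenous dose. A reader might infer from step 5 that low-eosinophil patients are likely to lose the whole effect. The documents do not support that: it is an extreme case, and they give no distribution of counts from which to take p. But an expectation of little loss is what the trial is meant to test, so it cannot stand in for a tighter criterion.

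**The quoted effect is on total LOS, the endpoint on LOS within 14 days.** A reader might infer that the cap inflates the false-positive rate. It does not for the endpoint as defined: in simulations with the margin set at the true capped difference, the error stayed nominal (2.3% to 2.7%). Judging the capped test against an uncapped excess mixes two estimands. The article also does not say where 1.2 came from.

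**A rationale may be in the full protocol.** That is fair, and its absence from the article is not held against the plan. No rationale alters the ratio of 1.2 to 1.22.

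**Conclusion.** The point holds as one of interpretation and should be fixed. The margin is 98% of the steroid effect on LOS that the protocol quotes, and six times the limit nearest zero. The treatment contrast is smaller than steroid against placebo, so 1.2 days is more lenient here than the ratio alone shows. Meeting it excludes an excess of 1.2 days or more. It does not establish preserved steroid benefit or an uninfluenced outcome.

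The ratios rest only on figures printed in the article. The 0.37 days and the power figures also assume SD 3.81 and 160 per arm. The 20% to 40% shares are illustrative, and the conclusion does not depend on them.

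A reader might infer that the trial is undersized. It is not: 320 is right for the margin chosen.

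**What to change.** Keep 320 patients, the endpoint and the test. Before any comparison by arm is seen:

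1. In the aim (Abstract and the end of Previous research), the Objective and the statistical section, state success as: *an increase in LOS within 14 days of 1.2 days or more is excluded*. Do not infer from it that the outcome is not influenced or that the steroid benefit is preserved.
2. Pre-specify that the upper 95% limit is reported next to the quoted 1.22-day effect and its interval.
3. Pre-specify a supplementary reading of that limit at about 0.6 days, labelled as a convention (half the point estimate). State its power: about 29% with SD 3.81, somewhat higher if the cap lowers the SD. Note that 0.6 is still three times the 0.2-day limit, so meeting it would not by itself prove that the benefit is preserved.

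The cost is a more modest claim and some redrafting. No patients, visits or treatment rules change, so it can be done although recruitment began in August 2016.
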